Probiotics may be a promising option for improving common symptoms of several brain and psychiatric diseases. While the gut microbiota has been of great interest in animal models in recent years, evidence for its effect on memory, mood, or movement in humans is still scarce, as summarized by several recent reviews (Li et al., 2021; Salami, 2021; Klann et al., 2022; Mukilan, 2022; Xiang et al., 2022) or described in original papers (Marotta et al., 2019; Handajani et al., 2022). A probiotic supplement is responsible for memory retrieval in the case of memory impairment. Therefore, it could be of potential use in the treatment of neurodegenerative disorders such as mild cognitive impairment or Alzheimer’s disease (Mukilan, 2022). The interplay of gut microbiota and cognition has been the focus of recent research. Increasing evidence suggests that a healthy gut microbiota is crucial for normal cognitive processing. Some studies have focused on the effects of either gut microbiota or probiotic bacteria on the brain’s cognitive function in health and disease status (Salami, 2021). Indeed, the administration of tempeh-derived probiotics increased the cognitive domains of memory, language, and visuospatial function (Handajani et al., 2022). A study by Marotta et al. (2019) showed an improvement in depressive mood state, anger, and fatigue and improved sleep quality in the group using probiotics, while no between-group differences were found (Marotta et al., 2019).

A recent review summarized pre- and probiotic studies related to Parkinson’s disease in humans (Klann et al., 2022). They found out that human clinical trials investigating probiotic supplementation for treating or managing Parkinson’s disease are limited. Probiotics are thought to improve symptoms by altering the gut microbiota composition to reverse dysbiosis and disrupt inflammation-related pathways (Klann et al., 2022).

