##### Brief cognitive tests

Brief cognitive tests included the Clock Drawing Test (CDT), our newly developed the ALBA test, and a short cognitive battery (ABACO). The CDT was evaluated using our developed and validated scoring system called BaJa. It was weighted in favor of assessing clock hands and suppressing the contribution of the clock itself. It ranged from 0 to 5 points. The time of 23:20 was chosen as it is cognitively more difficult than 11:10 or 5:40, as proven in our report (Bartos et al., 2016). The CDT was used without modification in all testing sessions. The CDT was omitted in online testing.

The ALBA test is a newly developed three-minute examination of intentional and incidental short-term memory, which could differentiate patients with mild cognitive deficits from cognitively normal individuals. The innovative test paradigm was based on a recall combination of one short six-word sentence and six gestures. First, a participant was asked to remember a sentence. The following distraction included a demonstration of six gestures and their incidental and immediate recall. The final task was sentence recall (Bartos, 2019). Two alternate forms of the ALBA test are available with good comparable psychometric properties in the Czech Republic (Bartos and Diondet, 2020). Online ALBA was the same as the in-person one (Polanska and Bartos, 2022). A completed example of an ALBA form with detailed administration and evaluation instructions is shown in Supplementary Figure 1. The ALBA educational video is freely available at: https://www.youtube.com/watch?v=LyCuWc0-Gro.

Our in-house cognitive battery, ABACO, consists of five brief tests: (1) the Reading Encrypted Sentences subtest, (2) the sentence learning and recall, (3) verbal fluency test, (4) the PICture Naming and Immediate Recall (PICNIR), whose educational video is freely available at https://www.youtube.com/watch?v=cbJGtPG-nVA, and (5) the Five or Four-line test. Detailed information about them is in Supplementary material 3.

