##### A comprehensive battery of neuropsychological tests

The Rey Auditory Verbal Learning Test (RAVLT) is intended for verbal memory evaluation. The test includes immediate verbal memory (A1), learning performance as a sum of five trials (A1–A5), proactive interference (B1), retroactive interference (A5–A6), and loss after consolidation (A6–A7) (Bean, 2011). In the Czech Republic, there are three alternative versions of RAVLT to eliminate the practice effect due to retest (Preiss et al., 2012). In the current study, we used them in version order: one at T1, two at T3, three at T4, and one at T5 (Figure 2). Online RAVLT testing was the same as that done in person.

The Trail Making Test (TMT) included parts A and B. Part A was used to evaluate processing speed, attention, and visuospatial ability. Part B, in addition to the mentioned functions, also assessed mental flexibility as a part of executive functions (Oosterman et al., 2010; Preiss et al., 2012). As there was no alternate form of the TMT in the Czech Republic, we used the same form for each test. The TMT was replaced with phonemic verbal fluency tests starting with the letters NKP during the online testing.

The Digit Symbol subtest from the Wechsler Adult Intelligence Scale III (WAIS-III) assessed the processing speed (Kaufman and Lichtenberger, 2005; Preiss et al., 2012).

Category (animal) fluency tests in person and online and phonemic fluency tests with initial letters NKP during online testing were used to evaluate executive functioning, language, and semantic memory (Lezak et al., 2012). Each verbal test took 1 min.

Online testing also included the Digit Span subtest from WAIS-III, which measured short-term verbal and working memory capacity (Preiss et al., 2012).

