## Proposed analysis

Data on the cognitive outcomes of the participants will be analyzed separately for groups evaluated in person and online. The results of online participants were exploratory due to the low sample size. Biochemical, self-report, and physical fitness outcomes were collected in person for all participants and were analyzed together. Statistical analyses will be conducted using R or Statistica.

Descriptive statistics will be calculated for primary and secondary outcomes at each visit.

The analysis will proceed using a between-subjects unpaired *t*-test at each time point or using a within-subjects paired *t*-test to compare results between time points.

Additionally, we will include apolipoprotein E allele status and its influence on outcomes.

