**FIGURE 4 F4:**
[figure not shown]
Expected hypotheses of cross-sectional (inter-group) and longitudinal (intra-group) comparisons at different time points. We expect improvement following the 3-month administration of probiotics (Δ: H1a, H2b, H2, H3). We expect no favorable change following the 3-month administration of placebo (H1b: =, H2a: =/<). Finally, we expect group B ending with the probiotic arm will have better outcomes than group A ending with placebo arm at time point T5 because of different intervals from the probiotic use (6 months for group A and 3 months for group B).

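### The one-group before-after paired t-tests (H1a, H2b) are planned as evidence of probiotic improvement, but they cannot separate it from retest gain or, for H1a, from placebo response

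*Protocol article*

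**What the plan says.** Proposed analysis offers unpaired t-tests between the groups at each visit, or else "using a within-subjects paired *t*-test to compare results between time points". The two are joined by an 'or', and neither is named as the basis for conclusions.

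The Figure 4 legend divides the hypotheses into cross-sectional (between groups) and longitudinal (within a group). It states "We expect improvement following the 3-month administration of probiotics", listing H1a and H2b among others, and "We expect no favorable change following the 3-month administration of placebo", listing H1b and H2a. The figure itself is not available. From the legend and the treatment order under Trial design, H1a is read as group A from T1 to T3 and H2b as group B from T3 to T4.

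Power calculation says that the paired sensitivity (0.43 for all participants, 0.51 in person only) was computed for the smaller group.

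On test forms:
- For the Trail Making Test (TMT), "we used the same form for each test".
- For the Clock Drawing Test (CDT), "The CDT was used without modification in all testing sessions".
- The three versions of the Rey Auditory Verbal Learning Test (RAVLT) were given in a fixed order: "one at T1, two at T3, three at T4, and one at T5".

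**The concern.** A change inside one group is not a treatment contrast. The concurrent placebo sequence protects comparisons between groups; a paired test within one sequence makes no use of it.

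- **H1a.** Group A's baseline precedes any tablet. Its T1 to T3 change therefore contains the probiotic effect, the response to taking a tablet (relevant to self-report scales such as the GDS, BDI-II, BAI and VAS), and any gain from repeating the test.
- **H2b.** Group B has taken blinded placebo before T3, so its T3 to T4 change compares placebo with probiotic in the same people. Retest gain, form order and calendar period remain mixed with the effect.
- **Forms.** TMT and CDT are repeated unchanged. RAVLT versions differ, but version is tied to visit, so any difference in difficulty cannot be separated from time within a group.

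Expecting no change on placebo (H1b, H2a) does not repair this. Significance in one group and non-significance in the other is not a test of the difference between them. At stake is a favourable conclusion on the primary cognitive outcomes from a product that does nothing.

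**Working it through.** **1. What the paired test is.** Solving the noncentral t for d at 80% power and two-sided α = 0.05:

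| Test | n | d | Stated |
|---|---|---|---|
| Paired, all participants' outcomes | 44 / 45 | 0.432 / 0.427 | 0.43 |
| Paired, in person | 32 | 0.511 | 0.51 |
| Two-sample, all | 44 + 47 | 0.594 | 0.59 |
| Two-sample, in person | 32 + 40 | 0.674 | 0.67 |
| Paired, both groups together | 91 / 72 | 0.297 / 0.335 | not stated |

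The stated 0.43 and 0.51 fit one sequence group and not the whole sample. The planned paired test is therefore a one-group before-after test. With 72 in person and a smaller group of 32, the other has 40. The article does not say which of A and B is smaller.

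**2. False favourable rate with an inert product.** Assumptions, since the document gives no values: gain g, in SDs of the score, from retest or any other non-specific source; retest correlation r = 0.7.

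- Standardised change: dz = g / √(2(1 − r)). At r = 0.7 the divisor is √0.6 = 0.775, so g = 0.1 / 0.2 / 0.3 gives dz = 0.129 / 0.258 / 0.387.
- Noncentrality: dz × √n. For g = 0.2 and n = 32: 0.258 × 5.657 = 1.46.
- Probability that the noncentral t on n − 1 degrees of freedom exceeds the upper 2.5% point of the central t:

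| n | g = 0.1 | g = 0.2 | g = 0.3 | Applies to |
|---|---|---|---|---|
| 32 | 11% | 29% | 57% | in-person cognitive tests |
| 40 | 12% | 36% | 67% | in-person cognitive tests |
| 44–45 | 13% | 39–40% | 71–72% | pooled outcomes only, e.g. self-report |

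The nominal rate in this direction is 2.5%. With g = 0.2 and n = 32, letting r run from 0.5 to 0.8 gives 19% to 41%.

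One check needs no r. A non-specific change equal to the quoted sensitivity (0.43 SD of change at n = 44–45, 0.51 at n = 32) is declared significant about 80% of the time with no probiotic effect.

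**3. The alternative.** Simulation: 10,000 trials, A = 40, B = 32, no probiotic effect, no carryover, the same gain in both groups, gain here in SDs of change.

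| Gain, period 1 / 2 | H1a | H2b | Either |
|---|---|---|---|
| 0.2 / 0.1 | 23% | 8% | 29% |
| 0.3 / 0.3 | 46% | 37% | 66% |
| 0.5 / 0.25 | 87% | 28% | 91% |

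In the same runs, two-sided rejection by a between-group t-test on T1 to T3 change, or on T3 to T4 change, stayed between 0.049 and 0.053. Gain common to both groups cancels.

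**The case against.** **An unbiased test is already planned, and listed first.** The unpaired t-test at each time point compares groups that share retest history, form order and, at T3, tablet-taking. Shared gains cancel there. This is correct, and it limits the point: the probiotic effect is to be shown only partly by paired tests. It does not remove the point, because the 'or' sets no priority, the legend gives the within-group comparisons their own hypotheses, and no stated test contrasts change between groups.

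**The approach is described as explorative.** True (Discussion), but its declared aim is to find which measures change because of the intervention. A before-after test cannot show that.

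A reader might also infer stronger things that the document does not support:
- *That H2b also counts placebo response as effect.* T3 in group B already follows three months of blinded placebo.
- *That success is defined as A significant and B not significant.* The legend states expectations, not a decision rule.
- *That H1a is the most exposed because practice gain is largest at first retest.* The article says nothing on the size of practice gain by visit.
- *That the n = 44–45 rates apply to the cognitive battery.* Cognitive outcomes are analysed separately for in-person and online participants, and TMT and CDT were not given online.
- *That reuse of the first RAVLT version at T5 distorts these hypotheses.* T5 enters neither H1a nor H2b, and the hypothesis there is between groups given the same version.
- *That the Introduction's cited study, with within-group improvement "while no between-group differences were found", shows how this trial will be judged.* The null between-group result is disclosed, and the citation says nothing about this plan.

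**Conclusion.** The point holds in this form: H1a and H2b, as one-group before-after tests, cannot support a claim about the probiotic. H1a is open to placebo response and retest gain; H2b to retest, form-order and period effects.

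For in-person cognitive tests, an assumed gain of 0.1 to 0.3 SD at r = 0.7 raises the false favourable rate from 2.5% to between 11% and 67% per test, depending on the gain and on whether the group has 32 or 40 members. These are illustrations over an assumed range, not estimates for this trial. Unchanged forms are documented for TMT and CDT. For RAVLT the issue is fixed order, and unequal version difficulty is a possibility, not a documented fact. The mapping of H1a and H2b rests on the Figure 4 legend.

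**What to change.** In Proposed analysis and the Figure 4 hypotheses:

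1. Base any claim about the probiotic on between-group contrasts of change over the same interval, with confidence intervals. Main test: A minus B in T1 to T3 change (T2 to T3 for samples and fitness, whose baseline is T2).
2. Supportive test: a period-adjusted A versus B contrast of T3 to T4 change. Period gain common to both groups cancels. Without carryover, group A moves by −δ and group B by +δ, so the difference is 2δ and is halved to give the effect. State that with no washout, carryover can bias it.
3. Label the one-group paired tests (H1a, H1b, H2a, H2b) as descriptive.
4. In Power calculation, say that 0.43 and 0.51 are sensitivities for before-after change within one group, not for probiotic against placebo.

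Cost: rewording and a re-analysis of data already collected. The more favourable-looking paired tests no longer support a claim. For the main contrast, the quoted sensitivity moves from 0.43 to 0.59 (all participants) and from 0.51 to 0.67 (in person), in SDs of change.

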### Power calculation

Given our sample size, we will able to detect the effect size of Cohen’s d = 0.43 in the matched-pairs two-tailed *t*-test, assuming power = 0.8 and α = 0.05. This will be d = 0.51 in those tests when only in-person data could be used.

For between-group comparisons, we could detect the effect size of Cohen’s d = 0.59 in a two-sample two-tailed *t*-test, assuming power = 0.8 and α = 0.05. This would be d = 0.67, assuming the use of only in-person data.

All power calculations were performed in G*Power 3.1.9.7 Software (Faul et al., 2007). As we did not attain equal group numbers, the sensitivity of the matched-pairs *t*-test is computed for the smaller group. This means we could detect a slightly smaller effect size for larger groups than reported here.

## Anticipated results and hypotheses

Our hypotheses are visualized in Figure 4. We expected a logical and favorable change in the cognitive tests, psychological measures, surrogate biological markers, and other measures following the 3-month probiotic treatment. Participants with at least one apoE four alleles would have worse results and, therefore, may benefit from probiotics more.

**FIGURE 4 F4:**
[figure not shown]
Expected hypotheses of cross-sectional (inter-group) and longitudinal (intra-group) comparisons at different time points. We expect improvement following the 3-month administration of probiotics (Δ: H1a, H2b, H2, H3). We expect no favorable change following the 3-month administration of placebo (H1b: =, H2a: =/<). Finally, we expect group B ending with the probiotic arm will have better outcomes than group A ending with placebo arm at time point T5 because of different intervals from the probiotic use (6 months for group A and 3 months for group B).

## Discussion

We prepared the first 6-month clinical trial to explore the effect of human probiotics in individuals with possible memory deficits. The aim was to include younger elderly individuals between 55 and 80 years of age for several reasons. This population is more prevalent and has a higher frequency of memory impairment than younger people. In addition, they are at the right age for memory improvement and interventions before they get too old or develop dementia.

We believe that the best target population includes individuals who are neither cognitively healthy nor suffering from dementia. On the one hand, healthy cognitive status is not necessary to improve. It may result in ceiling results without being able to observe a change after any intervention. On the other hand, patients with dementia have an advanced pathological processes in their brains. Managing their cooperation in complex studies of this kind is likely logistically costly or virtually impossible (e.g., taking stool samples in a standard manner to special test tubes within a certain time), and their comorbidities might affect the resulting data. Thus, individuals with mild memory deficits are ideal candidates for studies of probiotic effects. They need to improve their memory, and a positive change in test scores and other measures could be seen. However, it is problematic to find such individuals, motivate them to cooperate long-term, and achieve sufficient participant numbers after the exclusion of those with confounding factors (brain, psychiatric, and gastrointestinal diseases, among other conditions). This is highlighted by the fact that 724 individuals interested in our probiotic study using the electronic questionnaires were reduced to 91 (13%) eligible participants only, i.e., a ratio of eight interested persons to one included person in the study.

We chose an intervention using probiotics and prebiotics. A relationship between the gut microbiota and brain functions is considered in several diseases or conditions (Marotta et al., 2019; Salami, 2021; Handajani et al., 2022; Klann et al., 2022; Mukilan, 2022; Xiang et al., 2022). If proven effective, this natural way would be an easily feasible approach to prevent or postpone more pronounced memory decline or improve mood or anxiety in the elderly. In our comprehensive study, we decided to explore different aspects of brain functioning, physical performance, and blood, urine, and stool changes in response to probiotics with prebiotics. We use an explorative approach to determine which measures are influenced due to the intervention. We chose a crossover study design to ensure active intervention for each participant, which may achieve higher compliance and allow us to use each participant as a control for their own scores.

Probiotic treatment was intended for 3 months. A longer interval would prolong the duration of the study, make the trial more logistically complicated, and decrease participants’ compliance with the study. Three months of treatment was used in another related study (Handajani et al., 2022). The duration of our grant support also limits us. Our study was extended to 9 months for additional examinations to see the long-term effect of the intervention in a subset of participants.

The number of assessments and two types of tablets with a change after 3 months required careful management and sufficient and different personal resources and skills, facility equipment, and expert experience in many disciplines. We balanced recruitment with examinations and space capacities. This was the reason for establishing two centers for performing the study and limiting the number of participants included. Unfortunately, the COVID-19 pandemic complicated such a comprehensive clinical trial. Some participants refused to come to in-person assessments. The online testing had to be prepared for a relatively small group. Changing personal assessments to online ones might be an innovative approach to testing if a positive signal will be proven even in our small subgroups.

Our clinical trial has several strengths and limitations. First, we prepared a long list of inclusion and exclusion criteria to select appropriate candidates without present or previous brain, neurological, psychiatric, or gastrointestinal diseases and additionally fulfilling other conditions (participation at regular intervals for 6 months, appropriate veins, self-collection of stool and urine, etc.). Second, we created time-efficient recruitment using the electronic questionnaire for data collection from interested volunteers. Third, their memory was evaluated using an electronic test to invite only those with the worst results. This effective type of preselection saves resources and ensures a relatively homogenous group. Fourth, another strength is the comprehensive evaluation of probiotics with many cognitive tests, questionnaires, visual scales, psychological measures, and biological samples involving unusual materials like stool and urine. Fifth, an advantage is the use of probiotics of human origin. Moreover, we add prebiotics to stimulate bacterial growth.

A limitation includes a highly selected study population due to a high number of eligible criteria. The reason was to reduce confounding factors during the trial. Thus, our conclusions cannot be generalized to patients with mild cognitive impairment or deficits. This group of patients should be the next target of a probiotic intervention, although their comorbidities might change outcomes.

In conclusion, we wonder whether manipulating gut microbiota *via* probiotics will favor health conditions in the elderly. This study aims to contribute to this attractive idea in line with the contemporary high interest in interactions between the brain and microbiota.

## Ethics statement

The studies involving human participants were reviewed and approved by Ethics Committee of the National Institute of Mental Health, Klecany and the Ethics Committee of the University Hospital Královské Vinohrady, Prague. The patients/participants provided their written informed consent to participate in this study.
